### Recruitment

Women with newly diagnosed GDM who are potentially eligible to participate in the study will be given a study flyer. When attending clinic for standard GDM education, the Principal Investigator (PI) will explain the study and screen for eligibility, then invite eligible women to participate and provide written consent. The Participant Information Letter is provided in Supplement 1 and Participant Consent form in Supplement 2. Consent for data to be collected on the neonate will also be obtained.

Participant retention will be supported through undertaking study requirements at routine antenatal visits, complimentary parking, text reminders, supportive telephone contact from the PI between widely spaced appointments, and regular contact with the obstetric and midwifery team. Participants who withdraw consent to provide stool and urine samples will be given the option of providing fasting glucose samples.

### Randomisation

Stratified randomisation of participants based on pre-pregnancy Body Mass Index (BMI) category will be utilised. BMI categories are Healthy (BMI 18.5–24.9 kg/m^2^), Overweight (BMI 25–29.9 kg/m^2^) and Obese (BMI ≥ 30 kg/m^2^). A computer-generated random sequence was created by a statistician and repeating blocks of three groups per three BMI categories were used to generate group allocation order. Eligible participants will be randomised by the PI to the next predetermined group, sequentially as consented. Neither the participants nor the investigators will or can be blinded to the treatment allocated.

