### Intervention

#### Dietary intervention

All women will receive standard GDM dietary advice in line with evidence-based guidelines [2, 40, 43, 44]. Women will be encouraged to consume a minimum carbohydrate intake of 175 g per day, from mostly low glycaemic sources, distributed across the day over three meals and three snacks. The dietary advice will promote a low saturated fat intake and higher consumption of vegetables, fruit, dairy and whole grains.

After Baseline data are collected, women who are randomised to either of the two dietary intervention groups (RS Diet & RS Supp) will receive additional dietary education on consuming a high RS diet commencing on Day 3. All RS dietary education will be conducted by the PI who is an experienced Accredited Practising Dietitian (APD). A standardised teaching plan (Supplement 3) and education materials will be utilised (Supplements 4 & 5). Participants will be provided with written material including a Gut Feeling cookbook [45] and sample menus, as well as some non-perishable samples of high RS foods to allow for immediate adoption of the diet. Dietary RS will be measured at Baseline, Day 10 and Day 56 using 3-day weighed food records (Supplement 6). Evidence of compliance with the high RS diet will also be monitored via urine samples for metabolomic analysis and change in stool microbiota at the same timepoints. Participants will be asked to continue the high RS diet until the delivery of their child.

The RS education tools and strategies have been piloted in a non-pregnant population and achieved a median increase in dietary RS intake of ≥6.6 g RS per day (unpublished data). The typical intake of RS in Australian women aged 19–44 years has been estimated to range from 2.9–8.3 g per day [46]. Similarly, recent data from the United States estimated the mean daily intake of RS to be 1.9 g per 1000 kcal for women of this age [47], which would equate to 3.8–5.7 g per day.

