#### RS supplement

The RS Supp group will consume an RS supplement of high-amylose maize (HAMS) type 2 resistant starch. Participants will be given a 600 g tub of HAMS each fortnight, along with a 40 ml scoop. They will be instructed and provided with written material (Supplement 7) on how to prepare and incorporate the RS supplement into cool fluids or foods in their diet. As with all low-digestible carbohydrates, gastrointestinal (GI) discomfort is a known side effect of rapid introduction of RS, therefore, participants will introduce HAMS over a two-day adjustment period. They will be instructed to consume 1 scoop (20 g) per day for 2 days, taking half in the morning and the rest at night. Then, increasing to a dose of 1 scoop (20 g) morning and night for the remainder of their pregnancy. The RS supplement contains 40% RS type 2. The final amount of RS in the 40 g of HAMS per day will be 16 g, which is below the level of 45 g per day of RS supplementation that is known to be tolerated with minimal side effects, most of which are flatulence [48]. Intakes of up to 80 g RS per day have been tolerated without diarrhoea [48]. Those in the high RS diet plus RS supplement are unlikely to achieve this amount. Consumption and compliance of the RS supplement will be monitored by weight of unconsumed HAMS returned fortnightly. Participants will use a daily RS supplement diary to record intake as an additional measure of compliance. We have shown in a recent 2-week feasibility study, 100% compliance with consumption of the RS supplement and minimal GI side effects in 10 female participants with prediabetes or T2DM (unpublished). GI tolerance of the supplement will be measured via a daily bowel symptom diary for the first 10 days and Days 47 to 56.

Participants can withdraw from the study at any time for any reason. Participants will be withdrawn by the investigator if they commence antibiotics, steroids, metformin or if they can no longer comply with the study’s schedule of assessments (Table 1).

**Table 1 Tab1:** Participant measurements and collection summary

	Day 1	Day 3	Day 10	Day 28	Day 42	Day 56	Day 7 post-partum
Recruitment & consent	√						
Randomisation of subjects	√						
Attend clinic	√	√	√		√	√	
Self-monitoring blood glucose data collection		√	√			√	
FreeStyle Libre Pro application	√				√		
Questionnaires:							
medical Hx	√						
medication	√						
GI symptoms	√		√			√	
Quality of Life SF36	√		√			√	
Weight measured	√		√			√	

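### One unblinded PI recruits, allocates and teaches the diet from what read as blocks of three, and Day 1 randomisation precedes most of the Day 1–3 baseline record

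*Protocol article*

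**What the plan says.** Four statements in the protocol article bear on who knows what, and when.

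- **Recruitment.** At the routine teaching visit after diagnosis, "the Principal Investigator (PI) will explain the study and screen for eligibility, then invite eligible women to participate and provide written consent".
- **Randomisation.** A statistician produced a computer-generated sequence, stratified by three categories of pre-pregnancy BMI, in which "repeating blocks of three groups per three BMI categories were used to generate group allocation order". Then: "Eligible participants will be randomised by the PI to the next predetermined group, sequentially as consented". And: "Neither the participants nor the investigators will or can be blinded to the treatment allocated".
- **Dietary intervention.** The PI, a dietitian, gives all the RS education. It starts on Day 3: "After Baseline data are collected, women who are randomised to either of the two dietary intervention groups" receive it.
- **Table 1.** The row "Randomisation of subjects" is ticked on Day 1, the same day as recruitment and consent. Self-monitored glucose data, food records, diaries, stool and urine are first collected on Day 3.

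The overview of study design places Baseline over Days 1–3. The statistical analyses section takes the baseline fasting and post-prandial glucose from the first two days of self-monitoring. The primary outcome section also names a venous baseline fasting glucose, taken from the diagnostic OGTT.

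**The concern.** There are two separate weaknesses.

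**Predictable allocation.** The person who decides whether a woman is approached, judged eligible and consented also makes the allocation and then teaches the RS arms. That person knows every past assignment in each BMI stratum, even if the list itself is hidden. With small fixed blocks, this knowledge partly reveals the next arm. The study population section leaves room for judgement, because it excludes women whose psychosocial circumstances might impair adherence. A recruiter who expects the next place to be an RS arm could, without intending to, favour women who seem likely to comply. The planned covariates (age, pre-pregnancy BMI, parity, ethnicity) do not measure motivation, so the analysis could not reliably undo this. The target effect is modest: 0.3 mmol/L against an SD of 0.86, which is d = 0.35.

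**Baseline recorded after open allocation.** If the arm is assigned on Day 1 and nobody is blinded, eating, self-testing or symptom reporting over Days 1–3 can respond to the known arm. Those records are the reference for change in self-monitored glucose, RS intake, bowel symptoms, stool microbiota and faecal SCFA. The article holds back RS education until after Baseline, presumably to keep the baseline clean, and Day 1 randomisation works against that.

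**Working it through.** The article gives no figure for predictability, so there is none to reproduce.

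**Inputs**
- Three arms, three BMI strata, and blocks as described under Randomisation.
- Planned total of 90 women (Sample size).
- Assumption: block size is not stated outright. Three per stratum is the natural reading; six and nine are shown as a range.
- Assumption: the observer knows all past allocations in the stratum and guesses the arm with most places left in the block.

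**Block of three.** The chance of a correct guess is 1/3 for the first place, 1/2 for the second and 1 for the third:

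(1/3 + 1/2 + 1)/3 = 0.611, and 0.611 × 90 = 55 women.

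The last place in each block is certain: 90/3 = 30 women. At least one arm is ruled out for two places in three, which is 60 women. If the strata do not fill whole blocks (for example 20, 30 and 40 women), 6 + 10 + 13 = 29 are certain and the guess rate is 60.4%.

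**Larger blocks.** An allocation is certain when all remaining places belong to one arm, so the expected number of certain places is the expected length of the run of identical arms that ends the block.
- Block of six: 1 + 1/5 = 1.2 places; 1.2/6 = 20.0%.
- Block of nine: 1 + 2/8 + (2/8)(1/7) = 9/7 places; (9/7)/9 = 14.3%.

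The correct-guess rates come from an exact recursion over the places left in the block.

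| Block size per stratum | Correct guesses | Of 90 | Certain | Of 90 |
|---|---|---|---|---|
| Chance alone | 33.3% | 30 | 0% | 0 |
| 3 | 61.1% | 55.0 | 33.3% | 30.0 |
| 6 | 56.1% | 50.5 | 20.0% | 18.0 |
| 9 | 53.2% | 47.9 | 14.3% | 12.9 |

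**Randomly mixed blocks of 3, 6 and 9.** A simulation with 30 women per stratum, guessing the least-used arm so far, gives about 54.6% correct. The guess rate falls only modestly from 61.1%. The main gain is that the observer no longer knows where a block ends and so is less often certain.

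**Timing, item by item**

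| Baseline item | When obtained | Relative to Day 1 randomisation |
|---|---|---|
| Venous fasting glucose | Diagnostic OGTT, the eligibility test | Before |
| GI questionnaire, SF-36, weight | Day 1 | Not stated; may be before |
| Self-monitored fasting and post-prandial glucose | Mean of the first two days | Cannot be complete before |
| Food record, bowel diary | Days 1–3 | Cannot be complete before |
| Stool, urine | Listed at Day 3 | After |

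**The case against.** The case on the other side has real force, and much of it limits the point.

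- **The venous baseline is safe.** A reader might infer that every change-from-baseline comparison is compromised. The article does not support that: the OGTT value precedes consent and cannot respond to the arm. It does nothing, however, against selection at entry. The article also uses the self-monitored baseline in its model; which of the two serves the primary analysis needs reconciling.
- **The block wording is loose.** Three per stratum is an interpretation. Blocks of nine would lower the figures to 53% and 14%, still well above chance. One could also read it as a single order repeated throughout, which would be fully predictable, but the article describes a computer-generated random sequence.
- **Concealment may be in the full protocol.** A reader might infer that the PI holds the list and knows every allocation. The article does not say who holds it, and a condensed article need not. No weight is placed on this. Sealed envelopes would not remove what past allocations reveal.
- **Early RS eating is not shown.** RS teaching and materials come on Day 3, all women receive the same standard advice before that, and the article does not say outright that women learn their arm on Day 1. That they could is inferred from Table 1 and the absence of blinding.
- **A guess rate is not a bias estimate.** Steering would require deferring or excluding women at a routine education visit within a limited gestational window, and venous glucose is a laboratory measure. This is correct, and it is why the point stops at opportunity.

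**Conclusion.** The concern holds in two limited parts.

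First, one unblinded person recruits, allocates and delivers the diet from small blocks. On the natural reading of three per stratum, about 61% of allocations are guessable and one third are certain; with blocks of nine, about 53% and 14%; by chance, 33% and none. These figures assume an observer who keeps track of past allocations within strata.

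Second, Day 1 randomisation means that the self-monitored glucose, diet, bowel diary, stool and urine baselines are completed or collected after open allocation. The OGTT fasting glucose is exempt, and the Day 1 questionnaires and weight may be.

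Neither part shows that bias has occurred or how large it would be relative to the 0.3 mmol/L target. Severity: should-fix, chiefly because the remedy is cheap and selection at entry cannot be reliably repaired in analysis.

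**What to change.** 1. **Move randomisation in Table 1 from Day 1 to the existing Day 3 clinic visit**, after baseline samples, food records and diaries are handed in and before RS education. State that the Baseline records close at that visit. The bowel symptoms section has the diary returned at Day 10 and Day 56, whereas Table 1 lists collection at Day 3; the Table 1 timing is the one this change needs. Women who leave between Day 1 and Day 3 would then no longer be losses after randomisation.
2. **Have the statistician regenerate the remaining sequence** with randomly varying block sizes within BMI strata (for example 3, 6 and 9). Have each allocation released by a person or system independent of the PI, only after eligibility, consent and baseline are recorded.

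The two should go together. Varying blocks alone leave about 55% of allocations guessable, because the PI still sees past assignments when teaching the diet. Some predictability will remain even with both changes.

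Cost: a new list, a simple release arrangement and a one-cell change in Table 1, with slightly less balance within small strata. No extra visit is needed.

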## Methods

### Overview of study design

An open-label, parallel-group design study will be used to investigate whether a higher RS intake from diagnosis of GDM changes the gut microbiome and improves glycaemic control compared with standard dietary advice. Educating women to consume a diet consistent with evidence-based recommendations for the dietary management of GDM [40] was chosen as the comparator group as it is safe for participants and this study aims to evaluate whether the interventions are more effective than usual care.

Participants will enter the trial at diagnosis with GDM between 24 and 30 weeks of gestation. Informed written consent will be obtained by the Principal Investigator (PI) prior to randomisation into one of three dietary treatment groups – standard dietary treatment for GDM (Control), a high RS diet (RS Diet) or a high RS diet plus an RS supplement (RS Supp). The dietary intervention will continue until delivery. Measurements will be taken at Baseline over Days 1–3 (where they will be between 24 to 36-weeks’ gestation), Day 10, Day 56 (approximately 36-weeks’ gestation) and 1-week after delivery (Fig. 1).

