#### Microbiota

##### Maternal gut microbiota

All participants will receive written information (Supplement 8) and be instructed on the procedure for collection and storage of the first stool passed in the day at Baseline, Day 10, Day 56- and one-week post-partum. Each participant will be provided with a cooler and ice bricks for storage and transportation of stool samples. Upon receipt, stools samples will be weighed to the nearest 0.1 g on an electric balance (A&D, Japan) then immediately stored in a − 80 °C freezer. Stools will be thawed at 4 °C then homogenized and aliquoted, then restored at − 80 °C until analysed for microbial composition and their SCFA metabolites. This procedure will be repeated for each time point.

Microbial analyses will be performed at the Western Australian Human Microbiome Collaboration Centre at Curtin University. DNA will be extracted using the QIAamp PowerFecal Pro DNA kit (Qiagen). Microbiome signatures will be generated using the Illumina MiSeq platform barcoded V4 primer (515–806) targeting a hypervariable region of the 16S rRNA gene. Polymerase chain reaction free (PCR-free) ligation protocol will be deployed for library building. Samples will be sequenced to a depth of a minimum 20,000 reads, which is sufficient to identify microbes to a genus/species level. Quality control samples and mock communities will be included in the analysis from sample collection to sequence analysis. Sequence read quality will initially be assessed with FastQC before demultiplexing and pre-processing by GHAPv2, an in-house tool. Cutadapt [53] will be used for the removal of all non-biological sequences. DADA2 [54] will then be used for quality filtering, error correction, amplicon sequence variants (ASVs) picking. A trained Naïve Bayes classifier will then assign ASVs to genus/species against a curated database of microbial reference sequences such as the Ribosomal Database Project (RDP) [55] or Genome Taxonomy Database [56].

An increase in RS consumption is known to alter the gut microbiota in non-GDM populations [37]. An alteration from Baseline in stool microbial composition in RS groups towards a symbiotic composition compared with the control group will indicate that the increased RS consumption affects the microbiota of a woman with GDM and would indicate compliance with the RS dietary intervention.

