#### Gastrointestinal tolerance

##### Bowel symptoms questionnaire

Mild gastrointestinal side effects are expected with a high consumption of RS. A GI symptoms questionnaire adapted from Francis [64] will be administered at Baseline, Day 10 and Day 56 (Supplement 11). The questionnaire contains a visual analogue scale between 0 and 100 for each of four symptoms, generating a total score of up to 400. Participant responses will be measured manually from the zero mark by the PI and converted to a score out of 100. Scores will be used to evaluate the effect of the interventions on GI comfort and function.

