#### Resistant Starch intake

##### Food records

All participants will be instructed by the APD to keep a 3-day weighed food record at Baseline (Days 1–3), Days 8–10 and Days 54–56 for assessment of mean RS intake (Supplement 6). Food records will be collected at the next study visit. Alternatively, participants can choose to log their food intake using the Research Food Diary app (Xyris Software, Queensland, Australia). To aid in the accurate measurement of food consumed, kitchen scales (Propert, China), metric measuring cups and measuring spoons will be lent to participants. Nutrient analysis of food records will be completed using FoodWorks 10 (Xyris Software, Queensland, Australia). Databases on RS content of foods are limited and RS content varies widely depending on cultivars, growing conditions, country of origin, food processing, preparation and storage methods, and methods of analysis [61]. Published RS values for individual foods vary widely. Therefore, a database created from the minimum and maximum RS values published by various authors [46, 68–70] has been created by Edith Cowan University researchers and will be utilised in this study to calculate RS intake. This database has previously been used for nutrition research [71].

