### Statistical analyses

Baseline demographic and outcome variables will be described and compared for differences between groups. Continuous variables will be described as mean ± standard deviation (SD) and nominal and ordinal variables as frequencies and proportions. All continuous variables will be examined for normality using the Shapiro-Wilk test. Descriptive statistics for non-normal continuous variables will be presented as median ± interquartile range (IQR).

FBG and PPBG will be monitored on the first 2 days and averaged to provide a Baseline measure of each outcome. These will be compared to those measured over the subsequent 8 days, and then again between Days 48 and 56, across the three dietary groups (Control, RS Diet and RS Supp) using linear mixed modelling with group-by-time interaction. Analysis will assess if a 0.3 mmol/L reduction is achieved. Demographic variables such as age, pre-pregnancy BMI, parity and ethnicity will be adjusted in the model. Statistical analyses will be performed using SPSS® (Statistical Package for Social Sciences, version 27 for Windows).

The number of PPBG excursions experienced by a participant per day between Days 4 to 10 will be examined and compared relative to the number determined at their Baseline over the first 2 days of the usual care diet. Generalised Mixed Modelling will be utilised to assess whether a dietary change reduces the frequency of PPBG excursions as compared with norm with adjustments for relevant demographic variables.

Different R packages and PRIMER 7 (Quest Research, NZ), a non-parametric statistical software package, will be used to assess change within and between groups for microbial composition. Distance Based Linear Modelling (DistLM) will be used to look for a correlation between change in stool microbiota or SCFA & measures of glycaemia.

Direct and indirect costs savings related to any reduction in insulin treatment or improvements in maternal and neonatal outcomes will be calculated from DRG codes, Weighted Activity Units (WAU) and the National Efficient Price (NEP) and reported [74].

Missing data will be treated in statistical analysis as missing and coded as 999 or left blank, so as not to affect the accuracy of the analysis. Prior to any statistical analysis, all data will be explored for outliers. Any outliers found will be cross-checked with the source file. Any true outliers will be checked with the clinician before being removed/left in the dataset.

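### The non-blinding statement is too broad: the unmasked PI measures the GI symptom lines, and outlier decisions, including those on FBG, may be made with the arm known

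*Protocol article*

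**What the plan says.** The Randomisation section states: "Neither the participants nor the investigators will or can be blinded to the treatment allocated". The same section gives allocation to the PI: "Eligible participants will be randomised by the PI to the next predetermined group, sequentially as consented". Under Dietary intervention, the PI also delivers all the RS education.

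Three other places bear on this:

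- **Bowel symptoms questionnaire.** Four visual analogue lines, each scored 0 to 100, give a total of up to 400. On scoring, the article says: "Participant responses will be measured manually from the zero mark by the PI and converted to a score out of 100". The scores are then used to judge how the interventions affect GI comfort and function.
- **Statistical analyses.** All data are screened for outliers before analysis, and any found are checked against the source file. Those that prove genuine are discussed with the clinician and then either removed or retained. The article gives no numerical criterion and does not say that the arm is hidden at this point.
- **Data management.** Identifiable data are coded and electronic data are de-identified. The article does not say whether the code conceals the arm.

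**The concern.** The sentence in Randomisation claims both that investigators will not be blinded and that they cannot be. The second claim is one of feasibility, and it does not hold for an investigator who only reads coded sheets or analyses a coded file. An open-label trial can still mask those steps, and this wording gives that up.

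Two kinds of result are at stake. The GI score is a between-arm comparison measured by the person with the closest involvement in the intervention. Outlier removal is a judgement, and it applies to every variable. The primary outcome is a venous laboratory glucose, so the assay itself is well protected. A value that the assay reports correctly can still be dropped afterwards by someone who knows which arm it belongs to.

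**Working it through.** The article gives no figure on masking to reproduce, and masking changes no input to the sample size. The check is mainly a comparison of roles.

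1. **Participants.** They know what they eat and whether they take a supplement. The statement is correct for them.
2. **The PI.** The PI randomises (Randomisation) and teaches the RS diet (Dietary intervention). The statement is correct for the PI.
3. **Measuring the GI lines.** This needs only a ruler and a sheet. Nothing in the task requires knowledge of the arm, yet Bowel symptoms questionnaire gives it to the PI. The step is unmasked by express statement, not by inference from silence.
4. **Deciding on outliers.** This needs the value, the source record and clinical plausibility. The arm is not needed. Statistical analyses involves a clinician and sets no condition on what that clinician or the analyst may see. Screening comes before analysis, which helps, but that does not hide the arm.
5. **Consistency with a later plan.** If the statistical analysis plan masks an analyst who counts as an investigator, it will contradict the sentence in Randomisation. The sentence therefore needs narrowing whatever that plan says.

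**A worst-case illustration for step 4 (assumed, not protocol figures).** Take two arms of 30 (the planned group size), normal data, no true effect and a two-sided 5% t-test. The least favourable values are deleted: the highest in the RS arm and the lowest in control. In 100,000 simulated trials:

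- no deletion: significant in favour of RS 2.6%, in either direction 5.1%
- one value deleted per arm: 9.1% and 9.9%
- two values deleted per arm: 20.7% and 21.0%

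If the analyst sees only coded labels, the direction of deletion cannot be aimed at RS. By symmetry, the rate in favour of RS is then half the either-direction rate: 9.9% / 2 ≈ 5.0% for one deletion and 21.0% / 2 = 10.5% for two. Coded labels thus remove the aim but not the either-direction inflation. That goes only if outlier decisions are fixed without sight of the groups. This is why the fix needs both coded labels and locking. The figures show how few deletions would matter if made in this way. They do not estimate what will happen in this trial.

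**The case against.** **For the participants and the PI, the sentence is accurate.** This stands, and the point does not dispute it.

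**Laboratory and statistical staff.** A reader might infer that nobody in the trial is masked. The documents do not support this. The sentence names participants and investigators only. Pathology, sequencing and urine metabolomics go to separate services, and nothing says their staff know the arm. A condensed article may leave their masking, and the statistician's, to the full protocol or analysis plan.

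**Open pipeline choices.** A reader might also point to the unnamed R packages, the choice of taxonomic database and the published minimum and maximum RS values, and calculate the error from picking the best of several pipelines. Those details are commonly left to the analysis plan. Such a calculation measures lack of pre-specification: an analyst holding A/B/C labels could pick the largest test statistic just as easily. It says nothing about masking and is not relied on here.

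**The GI lines.** Measuring a line is close to mechanical, and an error common to all arms cancels, so only a differential error biases the comparison. The marks are made by unmasked women, and masking the measurer does not change that. Both points stand and limit the gain. An assumed ruler error in millimetres would add nothing.

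**Feasibility and cost.** Food records list what was eaten, and RS intake is meant to differ by arm, so masking there will be partial. Data management speaks of coding data and does not mention samples. A claim that masking is free has no source; low cost is a judgement.

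**Conclusion.** The point holds in a limited form. The feasibility claim in Randomisation is too broad. As written, the plan allows arm-aware scoring of the GI lines and arm-aware decisions on outliers in any variable, FBG included. It does not show that either will be biased, and it does not show that laboratory staff or the statistician are unmasked.

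The bias cannot be sized from the article. The exposure is one secondary tolerance score and the discretionary exclusions. The second matters more because it reaches the primary analysis. The conclusion assumes that the clinician and the analyst would know the arm, which the article permits but does not state. This is a worthwhile, inexpensive safeguard and not a defect that undermines the design.

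**What to change.** 1. In Randomisation, limit the statement to participants and staff who deliver the intervention. Say which scoring and analysis roles are masked.
2. Have the GI lines measured from coded sheets that carry neither arm nor identity, by an existing team member other than the PI where possible.
3. Give the analyst the arms as A/B/C.
4. Make and lock all outlier and exclusion decisions, and the analysis code, before the arm labels are revealed. It is preferable to make the outlier decisions with no arm column at all. The clinician consulted should see the value and the relevant source data, not the allocation.

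The cost is a relabelling step, a few sentences in the protocol or analysis plan, and a small amount of someone else's time for the GI lines. The article does not identify who that would be. Masking will remain incomplete where food records, RS intake or supplement data reveal the arm, and the plan should say so.
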